## Methods/Design

### Design

Controlled trial with a random allocation of participants in two alternative branches:

1. Implementation of a multimodal psycho-educational program to improve quality of life in FM (intervention group).

2. Usual care of FM (control group).

Evaluation of treatment outcomes will be carried out at the patient level, with individual evaluation at baseline and 1, 2, 6, and 12 months after the beginning of the intervention.

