### Variables and instruments of measurement

The study protocol was approved by the research ethics committee of the Foundation Jordi Gol i Gorina (Barcelona) and consists of the following materials:

1. *Sociodemographic characteristics*: Gender, birth date, address, marital status, education level, work status.

2. *History of the illness*: age of onset, date of the first diagnosis, pharmacological treatments (oral antidepressants, benzodiazepines-hypnotics, muscular relaxants and non-steroid analgesic and anti-inflammatory medications) and non-pharmacological treatments (physical exercise, relaxation techniques, cognitive-behavioural therapy) received during the previous 6 months.

3. *Questionnaire on chronic medical condition*.

4. *Fibromyalgia Impact Questionnaire (FIQ-Spanish version) *[23]: Instrument that measures physical function, work, and well-being, and contains visual analogue scales (VAS) for pain, sleep, fatigue, stiffness, anxiety and depression. A total score may be obtained after normalization of some items (between 0–10) and adding them to the VAS. Total scores range between 0–80 (without job items), with a higher score indicating a negative impact.

5. *EuroQoL-5D questionnaire (EQ-5D – Spanish version) *[22]: Generic instrument of health-related quality of life. It has two parts: Part 1 records self-reported problems in each of five domains: mobility, self-care, usual activities, pain/discomfort and anxiety/depression. Each domain is divided into three levels of severity corresponding to no problems, some problems, and extreme problems. Part 2 records the subject's self-assessed health on a Visual Analogue Scale (VAS); it is a vertical 10 cm line on which the best and worst imaginable health states score 100 and 0, respectively.

6. *Client Service Receipt Inventory – adapted (CSRI – Spanish version) *[24]: questionnaire for collecting information about use of healthcare and social care services, other economic impacts (such as time off work due to illness) and socio-demographic information. The variant used in this study was designed to collect retrospective data on service utilisation during the first and last six months after the beginning of the treatment.

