### Statistical analyses

Data collected will be analysed using SAS statistical analysis software (SAS Institute Inc. 1999. v8.0, 4th ed) and employing both quantitative and qualitative techniques.

First, the intervention and control groups will be compared in order to verify that there are no significant differences between them in socio-demographic terms, clinical baseline data, etc. We shall use mean and standard deviation (SD) in continuous variables and percentages in categorical variables. For comparisons we shall use the Student-T test for continuous variables and the Chi-square test for categorical variables. Non-parametric tests may also be used.

Given that we have one between-groups factor with two levels (2 Groups: Intervention and Control) and one within-subjects factor with five levels (Baseline and 4 follow-up assessments: 0, 1, 2, 6, and 12), a 2 × 5 mixed factorial ANOVA will be performed to study the effect of the psycho-educational program on the quality of life. Then, between-subjects planned comparisons may also be used (post-hoc comparisons with independent samples T-test). If we observe differences between groups in quality of life prior to treatment, one-way analyses of covariance will be carried out using baseline scores as a covariate). In addition, we shall carry out a logistic regression analysis taking the groups as dependent variable (the target variable is a categorical variable with two categories: Intervention and Control) and the collected measures as independent variables. This analysis will let us to know the association between the intervention and the cost of the healthcare resources, controlling for the rest of variables.

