As the duration of the study is only 12 months, neither costs nor outcomes are subject to discounting [26]. Treatment costs during 12 months follow-up will be modelled by a multivariate gamma regression with a log link. Gamma modelling has been suggested as a suitable choice for analysing cost data, taking into account the skewing of the distribution of the cost data [27,28]. QALYs gained in the first and last six months after the beginning of the program will be approximated by measuring the area under the curve (Figure 1).

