**Figure 1 F1:**
[figure not shown]
Formulas for calculating the QALYs gained in the first and last six months after the beginning of the program.

In the Figure 1, d_0–6 _is the incremental treatment effect on change in EQ-5D utility score for the first 6 months and d_6–12_the incremental treatment effect on change in EQ-5D utility score for the last 6 months. These incremental treatment effects will be estimated using multivariate ordinary least squares regressions, adjusting for baseline differences among treatment groups. The covariates included in the models will be: age, gender, years of education, employment and marital status, baseline FIQ and EQ-5D utility scores, and type of medication prescribed. To address uncertainty in the ICUR sampling distribution, non-parametric bootstrapping with five thousand replications will be carried out for each treatment comparison [29].

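### The additional logistic regression of randomised arm on the collected measures gives no cost effect and, if follow-up measures enter, can hide a real saving or show an association where total costs are equal

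*Protocol article*

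**What the plan says.** In Statistical analyses, after the mixed ANOVA for quality of life, the protocol adds: "we shall carry out a logistic regression analysis taking the groups as dependent variable". The predictors are "the collected measures as independent variables". The purpose is stated outright: "This analysis will let us to know the association between the intervention and the cost of the healthcare resources, controlling for the rest of variables".

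Three other places bear on this:

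- Design: "Controlled trial with a random allocation of participants in two alternative branches".
- Variables and instruments of measurement: the service-use inventory was "designed to collect retrospective data on service utilisation during the first and last six months after the beginning of the treatment". Cost is therefore measured after randomisation.
- Cost-utility analyses: "Treatment costs during 12 months follow-up will be modelled by a multivariate gamma regression with a log link".

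Table 1 lists FIQ, work situation and treatment received at every follow-up visit, and EQ-5D at months 6 and 12. Nothing in Cost-utility analyses withdraws or limits the logistic regression.

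**The concern.** Arm is fixed by random allocation, and cost is what the programme may change. A model with arm as outcome returns the odds of having been allocated to the programme per unit of cost. That is neither a cost difference nor a cost ratio.

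The adjustment set does more harm. The collected measures include follow-up FIQ, EQ-5D, treatment received and work situation, and the programme is meant to improve the first two. Treatment received also feeds direct cost, since medication is part of it. Holding these fixed removes the part of a cost effect that passes through them.

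Cost-effectiveness is the second objective, and the Abstract hopes to show lower service use. The protocol has two analyses of arm and cost and no rule on which prevails. A reader could take the logistic result as the fully adjusted answer.

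**Working it through.** **1. Number of patients.** The protocol gives no figure for the logistic model, so I took the numbers from its sample size paragraph: difference 5 FIQ points, 12.1 (called a standard error, used as an SD), two-sided alpha 0.05, power 0.80, dropout 15%.

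n = 2 × (1.960 + 0.842)² × 12.1² / 5² = 91.93, so 92 per arm; 92 / 0.85 = 108.2, so 109. The stated 109 is reproduced. I used 92 completers per arm.

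**2. What the cost coefficient tests.** Let Z be arm, C cost, F follow-up FIQ and B baseline FIQ. If C is independent of Z given F and B, then P(Z | C, F, B) = P(Z | F, B), and the coefficient on C is zero. A programme that saves money only by lowering F meets this condition, so the model has nothing to detect. Conversely, if a saving through F is cancelled by a direct increase, total costs are equal but C still depends on Z given F, so the coefficient is not zero. Neither result needs simulation.

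**3. Size under assumed cost inputs.** The protocol gives no cost distribution and no link between FIQ and cost. Assumptions:

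- baseline and follow-up FIQ correlate 0.5, with SD 12.1;
- the programme lowers follow-up FIQ by 5 points;
- cost is gamma with shape 1 to 2;
- log mean cost rises 0.03 to 0.05 per FIQ point (0.025 for half mediation, 0 for none).

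True cost ratios:

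- Saving wholly through FIQ: exp(−0.03 × 5) = 0.86 to exp(−0.05 × 5) = 0.78.
- Half: exp(−0.025 × 5 − 0.125) = 0.78.
- None: exp(−0.25) = 0.78.
- Equal totals: a direct increase of 0.15 (slope 0.03) or 0.25 (slope 0.05) cancels the saving, so the ratio is 1.

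Models compared: logit of arm on cost, follow-up FIQ and baseline FIQ; and gamma log-link regression of cost on arm and baseline FIQ. Share of trials with p < 0.05 for the arm–cost term:

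| Scenario | True cost ratio | Reversed logistic | Gamma |
|---|---|---|---|
| Saving wholly through FIQ | 0.78–0.86 | 3–6% | 18–45% |
| Half through FIQ (shape 2) | 0.78 | 18% | 62% |
| None through FIQ (shape 2) | 0.78 | 60% | 66% |
| Equal total costs, opposing paths | 1.00 | 13–47% | 5–7% |

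The low ends of 18% and 13% come from slope 0.03 with shape 1. The other combinations give about 26–45% in the first row (gamma) and 23–47% in the last (reversed logistic). As one worked setting, slope 0.03 and shape 2 over 1,000 trials gave 5.0% against 27.6% for the fully mediated saving, and 23.7% against 6.0% for equal totals. Repeat runs moved the middle rows by up to four points.

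**4. Is reversal alone the fault?** With no follow-up FIQ in the model, the reversed logistic rejected in 4–5% of trials when total costs were equal. With baseline FIQ as the only covariate and a true ratio of 0.86, it rejected in 24%, against 26% for gamma. The distortion comes from adjusting for post-randomisation measures.

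**The case against.** **The protocol claims only an association, and a reversed logistic can test that.** This stands. With cost alone or with baseline covariates it is a valid test of no association. A reader might infer that arm as outcome is invalid in itself; step 4 shows otherwise. It still gives no effect on the cost scale.

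**The text does not say which time points enter.** This also stands. The collected measures include baseline sociodemographics and illness history, and entry of follow-up measures is what the wording allows, not what it states. But the set is not restricted to baseline, and all other variables are to be controlled.

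**The no-signal result is a worst case.** Correct. It is one end of a range that runs to 60% against 66% when nothing passes through the FIQ.

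**The analysis is supplementary.** Correct, and it sets the severity. A reader might infer that the cost-effectiveness result is compromised. It is not: the cost-utility section has its own gamma cost model, least-squares models for EQ-5D and a bootstrap for the ratio.

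Two further inferences lack support. Overfitting or separation cannot be judged, because no predictor count is given. The covariate list for the cost-utility models, "baseline FIQ and EQ-5D utility scores, and type of medication prescribed", leaves the timing of medication open. But it follows the EQ-5D regressions, is not said to enter the gamma cost model, and is a detail an article may leave to the full plan.

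**Conclusion.** The concern holds in this form. The logistic regression gives no effect on the cost scale. If follow-up measures enter as the wording allows, it can miss a real saving and can show an association where total costs are equal. Both directions follow from the model structure. The percentages rest on the assumed slope, gamma shape and degree of mediation, none of which is in the protocol, and should be read as a range. It should be fixed, but it is not critical: the main quality-of-life analysis, the sample size and the incremental cost-utility ratio do not depend on this model.

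**What to change.** Delete the logistic regression and the sentence stating its purpose. Name the gamma log-link model under Cost-utility analyses as the single analysis of the cost effect, with 12-month cost as outcome, arm as predictor and baseline covariates only. Report the arm difference in mean cost in euros, from model predictions, with a confidence interval.

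This takes a few sentences of text. It needs no new data and does not change the sample size. The only loss is an analysis whose question the gamma model already answers on the cost scale.

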### Cost-utility analyses

Societal cost perspective will be used for the calculation of costs. *Direct costs *are going to be calculated by adding the costs derived from any medication and use of health-related services (general practitioner sessions, specialized medical sessions, emergency room sessions, and hospital in-patient stay). The cost of medications will be calculated by determining the price per milligram during the study, according to the International Vademecum (Red Book) 2007–2009, including value-added tax. Total costs of pharmacological treatment will be calculated by multiplying the price per milligram by the daily dose in milligrams and the number of days receiving such treatment. Costs derived from the use of health-related services will be calculated considering the SOIKOS unit costs database (25). *Indirect costs *will be calculated considering the days under sick leave and multiplying them by the minimum daily wage in Spain for 2007–2009. Finally, *total costs *are going to be calculated by adding direct and indirect costs.

In Spain, the National Healthcare Service (NHS) is financed by the general taxes levied by the state. In the municipalities where the study is carried out, it is administered by the autonomous government of Catalonia. Medical visits and hospital admissions are fully covered by the NHS. Medications prescribed are fully covered for retired persons, and partially for those still employed. Sick leave requires a physician's authorization, and patients unable to work continue receiving most of their salary.

When performing cost-utility analyses, two or more therapeutical options are compared in order to determine which one is the best for maximizing the benefits in light of the available resources [25,26]. This is achieved by calculating the relationship between the costs of a given intervention (e.g. A) and its consequences, expressed in QALYs, compared with another (e.g. B). This relative value is called incremental cost-utility ratio (ICUR), and it expresses the relationship between the costs and effects of one intervention compared with another.

As the duration of the study is only 12 months, neither costs nor outcomes are subject to discounting [26]. Treatment costs during 12 months follow-up will be modelled by a multivariate gamma regression with a log link. Gamma modelling has been suggested as a suitable choice for analysing cost data, taking into account the skewing of the distribution of the cost data [27,28]. QALYs gained in the first and last six months after the beginning of the program will be approximated by measuring the area under the curve (Figure 1).

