Another key component in current treatment of FM is the education of patients concerning their illness [18-20]. The main objective of educational programs is to increase skills in coping and healthy behaviour on the part of patients suffering FM. Scientific evidence has demonstrated that intensive education programs (between 6 and 17 sessions) improve pain symptoms, fatigue, insomnia and quality of life. These improvements continue 3 and 12 months later [14]. Furthermore, educational programs increase patient autonomy, reducing at the same time the consumption of medicines and use of healthcare services. The total cost of the continuous use of healthcare services by FM patients has not been estimated in Spain, but data from the USA reveal an annual cost of $2,274 per patient.

To date, it has not been demonstrated in Spain whether a multimodal program, combining autogenic relaxation and active healthcare education, produces a significant improvement in the quality of life of patients with FM. In addition, we do not know whether a multimodal program is more cost-effective than the treatment usually provided to these patients.

With this background, then, the main objective of the present research project will be to determine whether a multi-component psycho-educational program for treating FM leads to better quality of life (measured with the FIQ and the EuroQol-5D) at 1, 2, 6 and 12 months, than the usual care provided in Catalan Primary Health Care. The specific aims are to assess the degree of pain perceived by fibromyalgia patients attending the multimodal program, as well as the total direct costs (medication consumption and visits to public or private healthcare professionals) and indirect (work days lost), and cost-effectiveness associated with this psychoeducational intervention, compared to usual care.

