### Intervention program

Participants from the intervention group will undergo a multi-component psycho-educational program that deals with FM based on available scientific evidence. It includes measures and instruments that can be employed within the Catalan Primary Health Care, whereas the participants from the control group will receive only the treatment prescribed by their physician.

The intervention program consists of nine 2-hour sessions delivered during a two month period. Participants will be allocated in groups with a maximum of 18 subjects per group. All sessions will take place at the PC centres Gava-2 or Viladecans-2. The contents of each session are displayed in Table 2.

**Table 2 T2:** Summary of the intervention program.

**Session 1: **General information. Expectations of the patients. History of the illness. Principal and secondary symptoms in FM. Physiological mechanisms involved in the genesis of pain.
**Session 2: **Relaxation training-I
**Session 3: **Diagnosis. Pharmacological and non-pharmacological treatments. Prognosis. Current model of health care in Catalonia. Units specialized in the treatment of FM.
**Session 4: **Relaxation training-II
**Session 5: **Strategies to increase self-esteem and regulate emotions. Pain experience and recurrent invalidation. Social support (family and friends).
**Session 6: **Relaxation training-III
**Session 7: **Holistic medicine
**Session 8: **Relaxation training-IV
**Session 9: **Benefits of physical exercise in FM. Qualitative assessment of the intervention program. Resolving doubts. Discussion concerning the strengths and weaknesses of the intervention.

In order to avoid conversations concerning the psycho-educational program among patients from different groups, we will remind the participants from the intervention of the condition that they are not allowed to talk about the program with those persons that are not attending their group. Before baseline assessment, an explanatory note addressing this important issue will be delivered to the patients participating in the program.

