## Discussion

FM is a chronic illness that seriously alters the well-being of patients [1-3,30]. One of the main expected contributions of the present project is that we will have the opportunity to assess not only whether a multimodal psycho-educational program is feasible in primary health care, but also whether it is more cost-effective than the usual care provided for FM in this context.

Although FM has an irregular course that causes oscillations in the patients' quality of life, the random assignment of the participants to the conditions will minimize the differences not produced by the intervention. Baseline comparisons between groups will permit detection of possible pre-treatment differences.

In our opinion, the application of the program in PC entails a low outlay because nursing personnel may be trained to develop the program, as in other recent educational programs developed for a number of chronic illnesses [31,32].

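### The cost formula has no term for delivering the psycho-educational program, so the ICUR favours the program by its full delivery cost

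*Protocol article*

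**What the plan says.** The protocol article builds the cost of each arm in its Cost-utility analyses section.

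- Perspective: "Societal cost perspective will be used for the calculation of costs".
- The rule for the direct part reads "going to be calculated by adding the costs derived from any medication and use of health-related services (general practitioner sessions, specialized medical sessions", and the list of services closes with "emergency room sessions, and hospital in-patient stay".
- Indirect costs "will be calculated considering the days under sick leave and multiplying them by the minimum daily wage in Spain for 2007–2009".
- Total costs "are going to be calculated by adding direct and indirect costs".

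The Intervention program section describes what only one arm receives: "The intervention program consists of nine 2-hour sessions delivered during a two month period", in groups of up to 18. Controls have usual care alone. The only remark on what the program costs is in the closing Discussion: "the application of the program in PC entails a low outlay because nursing personnel may be trained to develop the program".

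Two other places bear on scope. The Background gives, as a specific aim, "total direct costs (medication consumption and visits to public or private healthcare professionals". The instruments section and Table 1 (months 6 and 12) have the CSRI record social as well as healthcare services.

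**The concern.** An incremental cost-utility ratio compares what two options cost with what they yield. The Cost-utility analyses section itself describes the ICUR as relating an intervention's costs to its consequences. The numerator it then defines holds only later service use, medication and sick leave. The intervention's own cost is not in it.

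The missing item is not shared between arms. Leaving it out lowers the incremental cost by the same amount for every patient allocated to the program. The planned 5,000 bootstrap replications describe sampling uncertainty and cannot restore a cost that was never entered: each replicate carries the same shift.

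The result at stake is the second objective, cost-effectiveness. If the program is given no cost, it can look cheaper than usual care, or appear to dominate it, when the true difference is small or has the opposite sign.

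**Working it through.** **Reproducing the plan's own figure.** The article states no cost or ICUR. The figure that fixes the number of groups is 109 patients per arm (Setting and study sample). Its inputs are a difference of 5 FIQ points, 12.1 (called a standard error, read here as a standard deviation), two-sided alpha 0.05, power 0.80 and 15% dropout.

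- n = 2 × (1.960 + 0.842)² × 12.1² / 5² = 91.9, so 92 per arm.
- 92 / 0.85 = 108.2, so 109 per arm and 218 in total. This matches.

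**Is there a program term?** Comparing resources with the cost section:

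| Resource | Where described | In the cost formula? |
|---|---|---|
| Medication | Cost-utility analyses | Yes |
| GP, specialist, emergency, in-patient | Cost-utility analyses | Yes |
| Sick leave | Cost-utility analyses | Yes |
| Program sessions (leaders, training, room, materials) | Intervention program; Discussion | No |
| Social services | CSRI description; Table 1 | Not listed |
| Private visits | Background | Not stated either way |

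**Program resources, from the article.**

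- Contact time per group: 9 × 2 h = 18 h.
- Groups: 109 / 18 = 6.06. Six full groups hold 108 patients, so 7 are needed.
- Group-hours: 7 × 18 = 126.
- Per patient and per leader: 126 / 109 = 1.156, or about 1.16 h.

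**Cost per patient, with assumed unit costs.** The article gives neither the number of leaders nor an hourly cost. Assume one or two leaders at 25-60 euros per hour.

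- Low: 1.156 × 1 × 25 = 28.9 euros.
- High: 1.156 × 2 × 60 = 138.7 euros.

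**Shift in the ICUR.** Shift = omitted cost per patient / QALY gain. The gain is also assumed, at 0.02 to 0.05 QALY.

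- Smallest: 28.9 / 0.05 = 578, about 580 euros per QALY.
- Largest: 138.7 / 0.02 = 6,936, about 6,940 euros per QALY.

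Training, room and materials would add to this.

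**Direction when other services are also left out.** Let P be the omitted program cost and S any saving in omitted services in the intervention arm, both per patient. Incremental cost is then understated by P − S. For illustration, with P = 69 euros (one leader at 60 euros: 1.156 × 60 = 69.4):

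- S = 50 gives 69 − 50 = +19, in favour of the program.
- S = 100 gives 69 − 100 = −31, against it.

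The sign is therefore certain for P alone, and open once other services are included.

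**The case against.** **The program may be meant to be included.** The sessions take place in primary care centres and could be called a health-related service; the gamma model is for treatment costs over the follow-up year; and a journal article leaves detailed costing rules to the full protocol. This carries some weight, since nowhere is the program said to be excluded or priced at zero. But the service list is given as four named items, with no wording that marks it as examples, and the section goes on to sum direct and indirect costs to a total. That is a complete rule, and applied as written it omits the program.

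**The amount is small.** The Background cites a US annual cost of $2,274 per patient, beside which 29-139 euros is modest. That is so, but an ICUR depends on the difference between arms, not on the annual total, and a modest amount divided by a small QALY gain is no longer modest. The documents give no threshold, so it cannot be shown that a conclusion would reverse.

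**Stronger readings that a reader might infer.**

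- *All the omissions together favour the program.* Not supported. Both arms can use social services, and the abstract's Discussion expects lower use of them with the program; on that expectation, leaving them out hides a saving and works against it.
- *Private visits are excluded.* Not supported. The GP and specialist items are not limited to public providers. The section is silent, while the Background names private visits.
- *Smaller groups make the cost higher still.* Possible, but the article gives only a maximum of 18, so any smaller typical size is a guess.
- *A societal perspective requires the patients' 18 session hours to be valued.* That is a methodological choice; the section states its own rule for indirect costs.

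**Conclusion.** The point holds for the program cost. As written, total cost contains medication, four kinds of care and sick leave, and nothing for the program that separates the arms. Incremental cost is understated by the full delivery cost, and for a positive QALY gain the ICUR is biased towards the program. This conflicts with the declared societal perspective and with the section's own account of the ratio.

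The firm quantities are 7 groups, 126 group-hours and about 1.16 hours per patient per leader, given groups filled to 18. The money figures, about 29-139 euros per patient and 580-6,940 euros per QALY, rest on assumed hourly costs, number of leaders and QALY gain. They show scale and do not predict the trial's result.

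The gaps on social services and private visits are matters of scope to be reconciled, with no known direction of bias. The comparison on the FIQ does not use the cost formula and is unaffected.

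**What to change.** 1. In Cost-utility analyses, add a program line to direct costs for the intervention arm: leader time, training time, room and materials, divided over all patients allocated to the intervention and not only those who attend.
2. Use this total in the gamma cost model, the ICUR and the bootstrap.
3. Align the section with the Background and the CSRI description: say whether private visits are counted, and either cost the social services that are collected or give the reason for leaving them out.

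The cost is a simple resource log for each group and a short paragraph of costing rules. No new patient measurement is needed, because session number, session length and the group maximum are already fixed and the CSRI already records social services. The downside for the sponsor is a slightly less favourable ICUR from the program line. The effect of step 3 could go either way.

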### Forecast execution dates

Initial recruitment of patients: September 2007

Deadline for recruitment of patients: November 2008

Deadline for period of patient monitoring: December 2009

Publication of results: 2010

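### Medication is priced with VAT under a declared societal perspective, and drug prices and the wage span 2007–2009 with no common price year

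*Protocol article*

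**What the plan says.** All the valuation rules are in the Cost-utility analyses section of the protocol article.

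- Perspective: "Societal cost perspective will be used for the calculation of costs".
- Medication: "The cost of medications will be calculated by determining the price per milligram during the study", with the source given as "according to the International Vademecum (Red Book) 2007–2009, including value-added tax". The price per milligram is multiplied by daily dose and days of treatment.
- Health services (general practitioner, specialist, emergency, in-patient): unit costs come from the SOIKOS database. Neither a price year nor a VAT treatment is given.
- Sick leave: days are valued by "multiplying them by the minimum daily wage in Spain for 2007–2009".
- Total cost is the sum of direct and indirect costs, so VAT on drugs enters it.
- Discounting: "As the duration of the study is only 12 months, neither costs nor outcomes are subject to discounting".

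Under Forecast execution dates, recruitment starts in September 2007 and closes in November 2008, and the last entry for follow-up reads "Deadline for period of patient monitoring: December 2009".

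**The concern.** A societal costing counts resources used, whoever pays for them. VAT on a drug is a payment from the buyer to the state, and society as a whole is no poorer for it. The same section explains that the health service is tax-financed and fully covers prescribed drugs for retired people, so for those patients much of the VAT passes from one public account to another. A VAT-inclusive price suits a payer or patient viewpoint, and neither is the one declared. Because VAT is mentioned only for drugs, drug costs may also stand on a different basis from visits and admissions.

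The second part concerns the price year. Drug prices and the wage are tied to a three-year range, service costs to no year, and all are added together. The section names no year in whose euros the result is expressed. The no-discounting statement does not settle this: it concerns time preference within one patient's 12 months, not price change across the calendar span of the trial.

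At stake are the size of any between-arm difference in drug cost, and whether the ICUR can be read as an amount in a particular year's money.

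**Working it through.** The article gives no VAT rate, no drug share of cost and no rate of price growth, so there is no cost figure of its own to reproduce. The rates below are assumptions, shown as ranges.

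**1. VAT and the incremental drug cost.** Let ΔD be the between-arm difference in drug cost net of VAT, and v the VAT rate, taken as the same for all drugs.

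- Recorded difference = (1+v)·ΔD, so the overstatement relative to ΔD is v.
- Assumed v = 4% to 10%: overstatement 4% to 10%.
- VAT as a share of the recorded drug cost = v/(1+v): 0.04/1.04 = 3.8%; 0.10/1.10 = 9.1%.

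**2. VAT and total cost.** Let s be the drug share of recorded total cost, assumed 10% to 50%. VAT's share of the total = s·v/(1+v).

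- Low end: 0.10 × 0.038 = 0.4%.
- High end: 0.50 × 0.091 = 4.5%.

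**3. VAT and the incremental total cost.** Let ΔO be the between-arm difference in all other costs.

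- Recorded increment = (1+v)·ΔD + ΔO, so the absolute error is v·ΔD.
- If ΔD and ΔO have the same sign, the relative error is v·ΔD/(ΔD+ΔO), which is below v.
- If they have opposite signs and nearly cancel, the relative error can exceed v, but the absolute error is still only v·ΔD.
- The QALY difference in the denominator is unaffected, so the ICUR inherits the relative error of the incremental cost.

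**4. Price year.** With annual price growth g, an identical item differs by (1+g)^t − 1 between two dates t years apart. Assume g = 2% to 5%.

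- 2007 against 2009 prices, t = 2: 1.02² − 1 = 4.0%; 1.05² − 1 = 10.25%.
- The same follow-up day for a patient enrolled in September 2007 and one enrolled in November 2008, 14 months apart: 1.02^(14/12) − 1 = 2.3%; 1.05^(14/12) − 1 = 5.9%.
- Span from first recruitment to the end of monitoring, September 2007 to December 2009: 27 months, touching three calendar years.

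With no price growth these spreads are zero.

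**5. Does price change favour an arm?** Patients are randomised over the same recruitment period, so both arms accrue costs over similar calendar time. On average the price mix is the same in each. The consequence is extra between-patient variation and an undefined price base, not bias.

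**The case against.** The strongest defence has four parts.

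- **VAT is an open choice.** The article states it plainly, it records what the health service and the patient actually spend, and nothing in the article says that transfers are excluded. It is fair that the mismatch rests on what a societal perspective means, not on two sentences that cannot both be true. It remains a stated rule that does not fit the declared perspective, and not a detail left to a fuller plan.
- **Conversion to a base year may be in the full protocol.** This also stands in part. A reader might infer that the plan mixes three price years outright, or that every price follows 2007–2009. The text does not go that far. Only drugs and the minimum wage carry those years; the SOIKOS costs carry none. Unadjusted valuation at each date's price is the natural reading of pricing "during the study", but it is not spelled out, and the year range might only list the editions consulted.
- **The drug difference may be small.** The Abstract says prescribed medication was maintained in both groups, and VAT scales only the difference between arms. A reader might infer that the trial hypothesises lower medication use, so that VAT would flatter the program. The article does not support that: its stated expectation, in the Abstract's Discussion, is lower use of healthcare and social services, without naming medicines. Reduced consumption of medicines appears in the Background as a general finding on educational programs. Still, medication is a named cost component there and is recorded again at every follow-up in Table 1, so a difference is possible.
- **Nothing is shown to change a decision.** Costs are expected to be skewed and are handled by gamma regression and bootstrapping, and the price-year noise has not been set against ordinary between-patient variation. This stands, and it keeps the point minor.

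**Conclusion.** The point holds, as a minor one. Pricing drugs with VAT under a societal perspective counts a transfer as resource use and overstates any incremental drug cost by the VAT rate: 4% to 10% if the rate lies in that assumed range. Under an assumed drug share of 10% to 50%, VAT is about 0.4% to 4.5% of recorded total cost. The effect on total incremental cost and the ICUR is smaller than that on drug cost, provided drug and other cost differences do not largely offset each other, and it is probably minor.

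On price year, identical quantities may be valued differently by calendar date, by about 2% to 6% for patients 14 months apart and 4% to 10% between 2007 and 2009 price lists, under assumed growth of 2% to 5% a year. It would be wrong to infer that this biases the comparison; concurrent randomisation protects it. What remains is noise and an ICUR not expressed in a single year's euros.

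**What to change.** In the Cost-utility analyses section:

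1. State that medication is valued net of VAT in the societal analysis. If the amount actually paid is of interest, report VAT-inclusive prices as a sensitivity analysis labelled as payer perspective.
2. Name one price year and apply it to drugs, SOIKOS service costs and the minimum wage for every patient, whatever the date of use. Cost differences then reflect quantities only.

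This takes a change of wording and one fixed price table. It needs no new data, since doses, days of treatment, service contacts and sick-leave days are already collected. The downside is a slightly lower recorded drug cost.
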